### Instruments and measures

#### Basic information

Basic information of the study subjects, including sociodemographic information and clinical disease characteristics. Demographic information will include age, gender, education, religion, place of residence, marital status, monthly income, method of paying medical bills, occupation, and the patient’s relationship to the primary caregiver. Clinical disease characteristics will include disease stage, course, and primary treatment modality.

#### Outcome: Family resilience

The Chinese version of the Family Resilience Assessment (C-FRA) will be used to assess the family resilience level of the research subjects (Zhang et al., 2021). This scale was developed for family resilience of breast cancer patients and translated into Chinese. It has good reliability and validity in breast cancer patients. The scale contains 5 dimensions and 28 items measured on a 5-point Likert scale. The higher the score is, the better the level of family resilience. Cronbach’s alpha for this scale is 0.961.

#### Outcome: Coping style

The Coping Style Questionnaire (CSQ) will be used to assess the coping style of the research subjects (Xie, 1998). It has good reliability and validity in breast cancer patients (Xu and Fu, 2018). The questionnaire contains 2 dimensions and 20 items. The first 12 items are positive coping, and the last 8 items are negative coping. Each item is scored from 0 to 3. The total score is the standard score of the positive coping dimension minus the standard score of the negative coping dimension. A total score greater than 0 indicates that the individual has a mainly positive coping style, and a total score less than 0 indicates that the individual has a mostly negative coping style. Cronbach’s alpha for this questionnaire is 0.90.

#### Outcome: Social support

The Social Support Scale (SSS) will be used to assess the social support level of the research subjects (Liu et al., 2008). The scale has good reliability and validity in breast cancer patients (Liu, 2022). The scale contains 3 dimensions and 10 items. Items 1–4 and 8–10 each are scored from 1 to 4. Items 6 and 7 are multiple-choice questions, with 1 point for each option and 0 points for a mismatch. Items 5 A, B, C, and D options correspond to 1–4 points, respectively. A total score of 22 and below indicates a low level of social support, a score of 23–44 indicates a medium level of social support, and a score of 45–66 indicates a high level of social support. Cronbach’s alpha for this scale is 0.896.

#### Outcome: Family disease burden

The Family Burden Scale of Disease (FBSD) will be used to assess the family burden of disease in the families of the study subjects (Tsang et al., 2003). It has good reliability and validity in breast cancer patients (Feng and Wang, 2017). The scale contains 6 dimensions and 24 items. Each item is scored from 0 to 2. The standard score for each dimension is the total score for that dimension divided by the number of items in that dimension. A standard score greater than or equal to 1 indicates moderate or more family disease burden on this dimension. The higher the total score is, the heavier the family disease burden. Cronbach’s alpha for this scale is 0.956.

#### Outcome: Anxiety

The Self-Rating Anxiety Scale (SAS) will be used to assess the anxiety level of the research subjects (Tian et al., 2019). It has good reliability and validity in breast cancer patients (Zhou, 2014). The scale contains 20 items measured on a 4-point Likert scale. The cutoff value of the SAS standard score is 50 points: 50–59 points indicates mild anxiety, 60–69 moderate anxiety, and 70 points or more severe anxiety. Cronbach’s alpha for this scale is 0.777.

#### Outcome: Depression

The Self-Rating Depression Scale (SDS) will be used to assess the depression level of the research subjects (Tian et al., 2019). It has good reliability and validity in breast cancer patients (Zhou, 2014). The scale contains 20 items measured on a 4-point Likert scale. The cutoff value of the SDS standard score is 53 points: 53–62 points indicates mild depression, 63–72 moderate depression, and 73 points and more severe depression. Cronbach’s alpha for this scale is 0.782.

### Data collection

First, the researcher will introduce the purpose of the study to the patients and their families and establish a trust with them. After obtaining informed consent from patients and their families, their baseline data will be collected. Baseline data includes sociodemographic data, clinical disease characteristics, and psychosocial variables. Psychosocial variables include family resilience, coping styles, family disease burden, social support, levels of anxiety and depression. Investigators will measure psychosocial variables of participating families at four time points: baseline and 1 week, 1 month, and 3 months after intervention (Table 2). Participants will be assured that all data and intervention processes will be confidential. Only the main researchers will have access to the final trial dataset.

**Table 2 tab2:** Data collection note.

	Outcomes	Baseline	1 week post-intervention	1 month follow-up	3 month follow-up
Eligibility criteria	Demographic and clinical data	√			
Primary outcome	Family resilience	√	√	√	√
Secondary outcome	Coping style	√	√	√	√
	Social support	√	√	√	√
	Family disease burden	√	√	√	√
	Anxiety	√	√	√	√
	Depression	√	√	√	√

### Statistical analysis

Two investigators will enter and review data. SPSS23.0 will be used for data analysis with a one-tailed test and a significance level of 0.025. Descriptive analyses will be used for participants’ general data and the outcome variables, including means, standard deviations, and percentages. The t test or rank-sum test will be used for comparison if the baseline data of the two groups are continuous variables, and the chi-square test will be used for comparison if they are categorical variables. The effect of the intervention program will be assessed by observing changes in family resilience, coping styles, family disease burden, social support, anxiety and depression levels in the intervention and control groups. If the intervention effect within the group conformed to a normal distribution, the paired t test was used for evaluation; otherwise, the Wilcoxon rank-sum test was used. Repeated measures ANOVA will be used to assess the effect of the intervention at different time points between groups. AHP, multivariate adjustment analysis, and propensity score analysis will be used to control for confounding factors confounding the study results.

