### Sample size

Study sample size calculated by PASS15. Based on previous survey results (Lim and Han, 2013), family resilience measured by the Family Resilience Index (FHI) changed by 0.29 points before and after the intervention with a statistical power of 0.9, 2.5% significance, and using a one-tailed test to calculate a sample size of 36 families in each group (72 families in total; McCubbin et al., 1996). Assuming a 10% dropout rate in the intervention, each group would need to include 40 families (80 families in total). The sample size calculation formula is as follows:

$$n=\frac{{\left({Ζ}_{\alpha }+{Ζ}_{\beta }\right)}^{2*}2\sigma^{2}}{\delta^{2}}$$

A series of measures will be taken to reduce attrition during the intervention. First, during the intervention recruitment phase, the patient’s attending physician or other medical staff will be invited to answer the patient’s and family’s concerns to increase participants’ trust in the program. Second, a WeChat group will be established where researchers answer questions and share disease-related knowledge with participants. The third is to invite breast cancer treatment experts and nursing experts to control the quality of the entire intervention process, and timely answer questions from patients and their families about disease treatment and care. Fourth, during the intervention, participants can get in touch with the research team to get answers to any difficulties involved in the implementation and application of the intervention content. Finally, at the end of the program, the research team will present the participants with a nice gift to express their gratitude.

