### Randomization

Eighty random numbers will be generated by a computer and randomly divided into an intervention group and a control group with a distribution ratio of 1:1. The assigned numbers will be sealed in 80 opaque envelopes. Recruiters will enroll research subjects who meet the research conditions, agree to participate in the research, and sign an informed consent form. Subjects will randomly draw envelopes, enter their assigned groups, and have baseline measurements taken. Participant recruitment and assignment will be done by two independent researchers, blinding participants, recruiters and data collectors.

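### The blanket one-tailed 0.025 rule has no meaning for the 3-df group-by-time F test, so the threshold for the main between-group analysis is undefined and may be stricter than the one behind the sample size

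*Protocol article*

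**What the plan says.** The Statistical analysis section of the protocol article gives one level and one sidedness, not limited to any particular test: "SPSS23.0 will be used for data analysis with a one-tailed test and a significance level of 0.025". It then lists the tests:

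- t, rank-sum or chi-square tests to compare the groups at baseline;
- paired t or Wilcoxon tests within groups;
- for the between-group effect, "Repeated measures ANOVA will be used to assess the effect of the intervention at different time points between groups".

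The Data collection section and its Table 2 give four time points: baseline, then 1 week, 1 month and 3 months after the intervention. The Hypotheses section is directional: family resilience is expected to be higher with the intervention than without it.

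The Sample size section takes a score that "changed by 0.29 points before and after the intervention" and plans "with a statistical power of 0.9, 2.5% significance, and using a one-tailed test to calculate a sample size of 36 families in each group". It uses the usual formula for two means and raises 36 to 40 per group for 10% dropout. It gives no SD.

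**The concern.** The level and sidedness agree between the Sample size and Statistical analysis sections. The difficulty is that the main between-group test cannot use them. An F test on several degrees of freedom pools departures in every direction, so it has no upper or lower tail in the sense of better or worse. The article does not say whether its p-value is to be read at 0.025, read at 0.05 or halved.

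Two things are at stake. First, reading the p-value against the written 0.025 imposes a stricter criterion than the one the trial was sized for. Second, the choice stays open until the data are seen. An ANOVA p-value of 0.04 fails at 0.025, passes at 0.05, and passes at 0.025 if halved to 0.02. For the primary outcome that should be settled beforehand.

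**Working it through.** **Inputs from the article.** Difference δ = 0.29; one-sided α = 0.025; power 0.90; n = 36 per group; 1:1 allocation; 10% dropout; 2 groups; 4 visits.

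**Assumptions (not in the article).** The SD is back-solved from n = 36. For the ANOVA: equal correlation ρ between all pairs of visits (0.3, 0.5 or 0.7), no difference at baseline, and 0.29 at each of the three later visits.

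**1. The article's own figure.** The formula is n = (Zα + Zβ)² · 2σ² / δ², with Zα + Zβ = 1.9600 + 1.2816 = 3.2415 (unrounded terms). Without σ, the 36 cannot be reproduced independently. Solving for σ:

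- σ = 0.29 × √(36/2) / 3.2415 = 0.3796, so d = 0.29 / 0.3796 = 0.764.
- The smallest σ that still rounds up to 36 is 0.29 × √(35/2) / 3.2415 = 0.3743, so d = 0.775.

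One-sided 0.025 and two-sided 0.05 both use 1.96, so both give 36. Dropout: 36 / 0.9 = 40, which reproduces.

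**2. Simple two-group comparison, non-directional p-value read at 0.025.** The critical value rises from 1.96 to 2.2414.

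- Normal approximation, σ = 0.3796: Φ(3.2415 − 2.2414) = Φ(1.0001) = 84.1%, against 90%.
- Noncentral t, 70 df, σ = 0.3743 (which gives 90% at one-sided 0.025): 83.8%.
- Noncentral t, 70 df, σ = 0.3796: 82.7% (this SD gives 89.2% at one-sided 0.025).

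Restoring 90% at that threshold would take 43 to 44 per group, or 43 / 0.9 → 48 to 44 / 0.9 → 49 with dropout.

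**3. A 1-df effect can be directional.** With 70 df, the squared one-sided 0.025 t critical value is 3.978, which equals the 0.05 critical value of F(1, 70). A group main effect or a single contrast can therefore be tested one-sided at 0.025 with no change of threshold.

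**4. The ANOVA itself** (n = 36 per group, d = 0.764, d² = 0.5837).

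- Group main effect, F(1, 70): noncentrality = (0.75d)² × 36 × 4 / [2(1 + 3ρ)] = 23.64 / (1 + 3ρ).
- Group-by-time, F(3, 210): the squared deviations of (0, d, d, d) from their mean sum to 0.75d², so noncentrality = 18 × 0.75d² / (1 − ρ) = 7.88 / (1 − ρ).

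| ρ | Main effect at 0.025 | Main effect at 0.05 | Interaction at 0.025 | Interaction at 0.05 |
|---|---|---|---|---|
| 0.3 | 89% | 94% | 72% | 81% |
| 0.5 | 78% | 86% | 88% | 93% |
| 0.7 | 68% | 78% | 99% | 99% |

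Reading at 0.025 instead of 0.05 costs about 5 to 10 points for the main effect. For the interaction it costs about 9 points at ρ = 0.3, 5 at ρ = 0.5 and less than 1 at ρ = 0.7.

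**The case against.** The best defence is that the two sections agree. Both say one-tailed 2.5%, and taken at their word both mean a critical value of 1.96. The article nowhere says that F-test p-values will be compared with 0.025. This stands, so the power loss is conditional on one reading and is not a stated feature of the plan.

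A reader might go further and infer that a one-tailed 0.025 level cannot be used with repeated measures ANOVA or chi-square tests at all. The documents do not support that. A 1-df effect can be read directionally without loss (step 3 of the working). The chi-square tests are planned only for categorical baseline variables, so they have no bearing on power for any outcome.

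A reader might also object that one-tailed testing prevents a worsening in anxiety, depression or burden from being declared. The hypotheses are openly directional, and the article plans descriptive means and SDs for the outcomes, so a worsening would still be visible. This adds little.

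Finally, a condensed article may leave the mapping of the level onto each ANOVA term to a fuller document. That would excuse silence. Here, however, the article does state a rule, and that rule has no meaning for the interaction test of the very analysis it names.

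**Conclusion.** The point holds as an undefined threshold for the main between-group test. The one-tailed rule is written for the whole analysis, and the 3-df group-by-time test cannot follow it. Reading that test at 0.025 would be stricter than the criterion behind the sample size.

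It would be wrong to conclude that the trial has 83–84% power in place of 90%. That figure applies only if a non-directional p-value is read at 0.025. It also describes a simple two-group comparison with 36 completing families per group, and it rests on an SD of about 0.374 to 0.380 inferred from that same number. The ANOVA's own power at 0.025 could be lower or higher: 72–99% for the interaction and 68–89% for the main effect over the assumed correlations of 0.3 to 0.7. The wording should be corrected before analysis; the defect does not invalidate the design.

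**What to change.** Make one of two changes, with the same wording in the Sample size and Statistical analysis sections:

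- state that all tests are two-sided at 0.05, with 95% confidence intervals; or
- name a single 1-df between-group contrast on family resilience as the primary test, at one-sided 0.025, and state the level for the remaining tests separately.

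The first is simpler and gives every named test a valid threshold. Either way the critical value in the two-mean calculation stays at 1.96, so 36 and 40 per group do not change and the cost is wording only.

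Neither change by itself gives the 3-df interaction 90% power. At 0.05 it has about 81%, 93% and 99% for correlations of 0.3, 0.5 and 0.7. If the interaction is meant to be the primary test, its power should be worked out with a stated SD and a stated correlation between visits.

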### Hypotheses

The research hypotheses are as follows:

After the intervention, the family resilience level of the intervention group will be significantly improved compared with that before the intervention.After the intervention, the family resilience level of the intervention group will be significantly improved compared with that of the control group.After the intervention, other aspects related to family resilience in the intervention group, such as the family disease burden and anxiety and depression levels of patients and their families, will be significantly relieved, and the level of disease coping and social support will be improved accordingly.

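### The within-group analysis names an independent-samples test for paired data and labels an uncontrolled before-after change as an intervention effect

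*Protocol article*

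**What the plan says.** The Hypotheses section lists three hypotheses. The first is a comparison inside one arm: "After the intervention, the family resilience level of the intervention group will be significantly improved compared with that before the intervention". The second compares the intervention arm with the control arm. The third expects burden, anxiety, depression, coping and social support to improve in the intervention group and names no comparator.

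The Statistical analysis section introduces the within-group analysis with "If the intervention effect within the group conformed to a normal distribution" and continues: "the paired t test was used for evaluation; otherwise, the Wilcoxon rank-sum test was used". The between-group analysis is separate: "Repeated measures ANOVA will be used to assess the effect of the intervention at different time points between groups". All testing uses "a one-tailed test and a significance level of 0.025".

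The same section also gives the rank-sum test to the baseline comparison of the two arms: "The t test or rank-sum test will be used for comparison if the baseline data of the two groups are continuous variables". There it is suitable, because the arms are independent.

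The Data collection section fixes the structure of the outcome data: "Investigators will measure psychosocial variables of participating families at four time points: baseline and 1 week, 1 month, and 3 months after intervention". Each family therefore supplies its own before and after values.

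**The concern.** There are two separate defects in the same analysis.

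**Test name.** The paired t test and its stated alternative do not belong together. The rank-sum test treats the before and after values as two unrelated samples. Where a family's two scores are positively correlated, the test uses too large a null variance and its real error rate falls below the nominal one. An analyst who followed the text would run the wrong procedure whenever normality was rejected.

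**Meaning of the result.** The plan calls a one-arm before-after change an intervention effect and makes it the first hypothesis on the primary outcome. Under the Intervention section, baseline is taken before the first meeting, which is 1 week after surgery. The sixth meeting is at 6 weeks, and the first post-test follows 1 week after the programme ends, so about 7 weeks after surgery. Recovery over that period, or usual care (handbooks and a WeChat support group), could move the score without any contribution from the programme. The control arm exists to remove such influences, and hypothesis 1 does not use it.

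**Working it through.** **Inputs from the protocol article.** 36 evaluable families per group, raised to 40 for 10% dropout (Sample size); one-sided 0.025 (Statistical analysis); paired measurements (Data collection). The dropout step reproduces: 36 / (1 − 0.10) = 40.

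**Assumptions.** The documents give neither the before-after correlation r nor the size of any natural change. I take r = 0.3 to 0.7 and express change in SD units of the score.

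**Step 1: error rate of the rank-sum test on paired data.** Pairing shrinks the variance of the before-after contrast by a factor of about (1 − r), which the rank-sum test ignores. A rough guide to its true size is Φ(−1.96 / √(1 − r)):

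- r = 0.5: Φ(−1.96 / 0.707) = Φ(−2.77) = 0.0028.
- r = 0.7: Φ(−1.96 / 0.548) = Φ(−3.58) = 0.0002.

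This guide uses the ordinary correlation where a rank statistic needs the rank correlation, and it is too extreme at high r. Simulation with n = 36 gives:

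| r | rank-sum size | signed-rank size |
|---|---|---|
| 0.3 | 1.0–1.1% | about 2.4% |
| 0.5 | about 0.4% | 2.3–2.5% |
| 0.7 | 0.05–0.1% | about 2.3% |

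Lognormal (skewed) scores give nearly the same rank-sum sizes, 1.0% to about 0.1%. The result therefore holds in the non-normal setting where the fallback would be used.

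**Step 2: power where the fallback applies.** With normal data the paired t test is run, so a power comparison on normal data is not relevant. For lognormal scores (log-scale SD 0.8, r on the log scale, n = 36, 10,000 runs):

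| shift | r | rank-sum | signed-rank |
|---|---|---|---|
| 0.2 SD | 0.3 | 30% | 30% |
| 0.2 SD | 0.5 | 29% | 39% |
| 0.2 SD | 0.7 | 24% | 55% |
| 0.4 SD | 0.3 | 85% | 76% |
| 0.4 SD | 0.5 | 87% | 86% |
| 0.4 SD | 0.7 | 92% | 96% |

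With heavier skew (log-scale SD 1.0) and a 0.4 SD shift, rank-sum reaches 96–99% against 88–99% for signed-rank. At 0.2 SD and r = 0.7 it falls behind, 58% against 73%. Power has no fixed direction.

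**Step 3: hypothesis 1 with an inert programme.** The SD of the change is √(2(1 − r)), which is 1 at r = 0.5. The paired t statistic then has 35 degrees of freedom and noncentrality gain × √36 = 6 × gain. The chance of a significant result at one-sided 0.025 is:

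| natural gain | noncentrality | significant |
|---|---|---|
| 0.2 SD | 1.2 | 21% |
| 0.3 SD | 1.8 | 42% |
| 0.4 SD | 2.4 | 65% |
| 0.5 SD | 3.0 | 83% |

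**The case against.** **The controlled test is already in the plan.** Hypothesis 2 is a randomised comparison with its own analysis. This stands. A reader might infer that hypothesis 1 alone could carry an efficacy claim, or that the trial lacks a valid test of the programme. The documents say neither. What they lack is a sentence ruling out the first reading, while the label attached to the within-group change invites it.

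**The rank-sum entry may be a slip of the pen.** Possibly. It applies only if normality fails, and its error is conservative, so it does not create false positives. The text as written still directs the wrong test.

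**The wrong test need not cost power.** This stands. It is tempting to say that the fallback has low power, but the large losses appear with normal data, for which the plan uses the paired t test. With skewed data the answer depends on shift, skew and correlation.

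**Regression to the mean is not shown.** This also stands. A reader might add it to recovery and usual care, but it needs selection on an extreme baseline value, and the eligibility criteria set no threshold on resilience or distress.

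**The natural gains are assumed.** They are, and the documents do not even fix their direction. The Introduction describes reduced family intimacy and function after diagnosis as well as families that adapt and grow. A natural decline could equally hide a real benefit from hypothesis 1. Either way, the one-arm change does not isolate the programme.

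**Conclusion.** Both defects hold within limits. The named fallback is the wrong test for paired data: its one-sided error is about 1.1% to 0.1% instead of 2.5%, for n = 36 and assumed correlations of 0.3 to 0.7. No general statement about its power is justified. Hypothesis 1 and its label present an uncontrolled change as an effect. The 21% to 83% range shows how readily an inert programme could satisfy it, given an assumed gain of 0.2 to 0.5 SD and correlation 0.5; it is an illustration, not a forecast for this trial.

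The damage is confined to within-group claims: hypothesis 1, and hypothesis 3 where it names no comparator. The randomised comparison, the stated sample size and the data to be collected do not depend on this point. It should be fixed, but it is not a fatal flaw.

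**What to change.** 1. In Statistical analysis, replace the Wilcoxon rank-sum test with the Wilcoxon signed-rank test for within-group change. Keep the rank-sum test for the baseline comparison of the two arms.
2. Replace the label that calls within-group change an intervention effect with a neutral term such as change from baseline.
3. State that within-group results, covering hypothesis 1 and the parts of hypothesis 3 without a comparator, are descriptive, and that efficacy is judged on the between-group contrast under hypothesis 2.

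Hypothesis 1 need not be deleted. That would revise a stated hypothesis of a registered, ethics-approved trial, and the descriptive label is enough. The cost is a few sentences, with no change to sample size, visits or procedures.

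### In a 1:1 randomised trial of 80 families, the plan commits to baseline significance tests, an unexplained AHP and propensity scores to control confounding, and marks no analysis as primary

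*Protocol article*

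**What the plan says.** All of this is in the protocol article; no separate analysis plan is shown.

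- **Statistical analysis, baseline:** "The t test or rank-sum test will be used for comparison if the baseline data of the two groups are continuous variables", with chi-square tests for categorical variables. The general rule for the analysis is that "SPSS23.0 will be used for data analysis with a one-tailed test and a significance level of 0.025", and baseline comparisons are not exempted.
- **Statistical analysis, effect:** repeated measures ANOVA is named for the between-group comparison over time, with no covariates given.
- **Statistical analysis, adjustment:** "AHP, multivariate adjustment analysis, and propensity score analysis will be used to control for confounding factors confounding the study results". AHP is not expanded anywhere in the article. The three methods are not ranked against each other or against the ANOVA.
- **Study design and Randomization:** allocation is 1:1 from computer-generated random numbers in sealed opaque envelopes.
- **Basic information:** ten demographic items are listed, and "Clinical disease characteristics will include disease stage, course, and primary treatment modality". **Data collection** adds six psychosocial scores at baseline.
- **Timing of baseline:** Randomization puts the baseline measurement after the envelope is drawn. Data collection says only that it follows consent.

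**The concern.** The adjustment sentence reads as if it were written for an observational study. Randomisation makes the allocation probability known, so the three methods have no systematic imbalance to correct. One of them cannot be identified, and in its usual meaning it is not an adjustment method at all. Baseline tests ask whether chance produced a difference that, under proper randomisation, could only have come from chance. They are a poor guide to which covariates matter for the outcome.

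At stake are clarity and precision. A reader of the results could meet an ANOVA and up to three adjusted estimates of the same effect without knowing which one carries the conclusion. Meanwhile the simplest useful adjustment, for baseline family resilience, is not named.

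**Working it through.** 1. **Numbers available.** The plan reports that "Assuming a 10% dropout rate in the intervention, each group would need to include 40 families (80 families in total". Check: 36 / (1 − 0.10) = 40, which reproduces. The 36 cannot be checked because no SD is given. With the printed formula, δ = 0.29, one-sided 0.025 and power 0.90, n = 36 implies an SD of about 0.374 to 0.380. So there are 40 families randomised and about 36 evaluable per arm.

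2. **Baseline variables.** 10 demographic + 3 clinical + 6 psychosocial (anxiety and depression counted separately) = 19.

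3. **Baseline tests under correct randomisation.** If the tests are independent, P(at least one significant) = 1 − (1 − α)^k.
   - α = 0.025, k = 19: 1 − 0.975^19 = 0.38; expected number 19 × 0.025 = 0.48.
   - α = 0.05, k = 19: 1 − 0.95^19 = 0.62; expected number 0.95.
   - Gender is constant among patients, who are all women. If it is dropped, k = 18 and 1 − 0.975^18 = 0.37.
   - Coping, support, burden, anxiety and depression are probably correlated, which lowers the figure. The floor is 0.025, if all tests agreed completely.

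4. **Size of a propensity model.** The article does not say which variables would enter. With the 13 background variables there are 40/13 = 3.1 families per arm per predictor; with all 19, 40/19 = 2.1. Coding multi-level categories would lower both.
   - A null simulation (4000 trials per setting, 36 v 36, 19 independent normal covariates) used the fitted score as a covariate with ordinary standard errors. At assumed baseline–outcome correlations of 0.3, 0.5 and 0.7, the one-sided error was 0.0225, 0.010 and 0.0025 against a nominal 0.025.
   - This is conservative, so the cost is power rather than false positives. The runs gave numerical overflow warnings and any invalid result counted as non-significant, so these rates are indicative only.

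5. **Value of adjusting for baseline C-FRA.** Assume equal SDs at baseline and follow-up, correlation ρ, and one follow-up time. The variance of the group contrast is proportional to 2(1 − ρ) for change scores and 1 − ρ² for ANCOVA. The ratio is 2/(1 + ρ).
   - ρ = 0.5: 1.00/0.75 = 1.33. ρ = 0.6: 0.80/0.64 = 1.25.
   - Wider range: ρ = 0.3 gives 1.54 and ρ = 0.7 gives 1.18.
   - So 36 per arm on change scores matches about 27 (36/1.33) to 29 (36/1.25) per arm on ANCOVA. The correlation is not in the article.

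6. **Illustration of an open choice.** In the same simulation, a single prespecified ANCOVA had one-sided error of 0.023 to 0.025. Taking the smallest p from five analyses (unadjusted, baseline ANCOVA, all 19 covariates, only covariates with baseline p < 0.05, propensity covariate) gave 0.052 to 0.054.

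**The case against.** The strongest reply is that this is a condensed article. Covariate lists and the order of models usually sit in an analysis plan, and the ANOVA is already named for the between-group effect, so the adjustment sentence may describe supplementary work only. Much of this stands: a missing covariate list is no finding, and the supplementary reading is reasonable. It does not rescue what the text does state. An analysis plan could add covariates or a hierarchy, but it would not give a propensity score confounding by design to remove or turn analytic hierarchy process into an adjustment method. A propensity score can serve as covariate adjustment in a randomised trial with a short fixed list, but the purpose stated here is control of confounding.

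A reader might go further than the documents allow in five ways.

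- **That the adjusted result will be chosen after seeing the data, doubling the error rate.** Nothing says that baseline tests trigger adjustment or that the most favourable result will be reported. The figure of about 0.053 in step 6 shows what unrestricted choice could do; it is not a property of this plan.
- **That the baseline score goes unused, at a cost of 33–56%.** Those figures are 1/(1 − ρ²) at ρ = 0.5 and 0.6, against an analysis of follow-up scores alone. The ANOVA includes baseline as one of its four time points, so the change-score comparison in step 5 is the nearer one.
- **That multivariate adjustment is itself unsuitable.** It is sound when short and prespecified.
- **That randomised families will be discarded.** Matching is not mentioned, and neither is a model with all 13 or 19 variables.
- **That every baseline test has a null known to be true.** Six of the variables are questionnaire scores that the Randomization section places after the envelope draw. They could differ for reasons other than chance, although the article also states that participants are blinded. Significance tests would not settle this.

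**Conclusion.** The point holds in limited form. The plan commits a randomised trial to methods that do not fit its design (a propensity score to control confounding, and baseline significance tests) and to one that cannot be identified (AHP). It does not say which analysis is primary.

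The 38% for at least one false imbalance at 0.025 rests on 19 independent tests and is an upper figure if they are positively correlated. The instability of a propensity model is conditional on many of the listed variables entering it. The 25–33% gain from adjusting for baseline C-FRA rests on assumed correlations of 0.6–0.5, equal SDs and a single follow-up time. None of this undermines the randomised comparison itself. It is an inexpensive improvement that should be made, not a fatal defect.

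**What to change.** In the Statistical analysis section:

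- Delete AHP, or replace it with the name of the method meant.
- Delete the propensity score analysis and the baseline significance tests; present baseline data descriptively by arm.
- Name one primary between-group model for C-FRA, either ANCOVA or a repeated-measures model of the post-baseline scores, with group and baseline C-FRA as covariate.
- Label the repeated measures ANOVA and any further covariate adjustment as sensitivity analyses.

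Reconcile Randomization with Data collection by stating that baseline scores are collected before allocation is revealed, so that allocation cannot affect the covariate. Recruiting hospital may be added as a covariate, but this is optional: no stratification by hospital is described.

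The cost is a change of wording and less analysis. Baseline C-FRA is already scheduled in Table 2, so no new data are needed. The only operational change is to the order of baseline measurement and envelope opening, if practice follows the Randomization text.
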